### **9.5.3 Development**

In August and September 2021, we convened two remote intervention development workshops comprised of patients, carers, physiotherapists, triallists, implementation and behaviour change scientists, as well as a panel of experts in rehabilitation for patients after hip fracture from the UK, Denmark, Norway, Spain, USA, Canada, Brazil and Australia (n=20 participants). At the workshops, we presented the rationale and key question (*what intervention would enable older adults to take part in activities outside the home after hip fracture?*), data/results from existing evidence, including results of our two systematic reviews, outline of current UK provision, proposed theoretical frameworks, and draft programme theories and logic model. We then followed a nominal group technique inviting participants to generate intervention ideas silently prior to sharing in a round-robin format. All ideas were documented. Participants sought and provided clarification on shared ideas. Top ideas were then prioritized for incorporation into the subsequent draft programme theories and logic model (Figure 2) which were finalised after the second workshop.

### **9.5.4 Programme theories**

1. For older adults who were mobile outdoors prior to hip fracture, health-related quality of life post-fracture is enhanced by regaining outdoor mobility;
2. Achievement of physical, psychosocial, and cognitive capability to go outdoors requires tailored, structured, and graded support with mechanisms to monitor and preserve gains.

### **9.5.5 Intervention Description**

The intervention will start around 30 days after a participant returns home and end when their mobility end goal (patient and therapist shared goal) is achieved, or six visits have occurred, or 12 weeks have passed – whichever comes first. It will be delivered by therapists (physiotherapists/ occupational therapists/ therapy assistants). Online intervention training will be provided to treating therapists prior to delivery. To enable fidelity assessment, therapists will audio record intervention sessions, with participants’ consent. Audio recordings will be supplemented by study-specific ‘intervention’ questionnaires completed by the physiotherapist/occupational therapist/therapy assistant after each session with a participant.

Intervention participants will receive usual care (see 9.5.6) and:

#### **9.5.5.1 Motivation – social support**

Participants will be provided access (via therapist held tablet) to a video of older adults who incurred hip fracture sharing their experience of recovery. Therapists will also provide participants with a piece of paper with a Kings College London SharePoint server website link written on it, should

participants wish to watch the video again later in their own time. The content of the video includes discussion by four older adults about their *capability*, *opportunity*, and *motivation* to generate and maintain their desired behaviour of outdoor mobility (including walking, taking public transport) after hip fracture. More specifically, the video targets motivation through the behaviour change techniques *opportunity for social comparison* and *social support (practical, general, and emotional)*.

### 9.5.5.2 Goal-orientated mobility programme

Participants will have a telephone call/MS TEAMS call with a therapist to set an outdoor mobility programme goal. This goal will be meaningful to the participant and be deemed achievable within the scope of the programme by the therapist.

The 'programme goal' will be broken down into a maximum of four 'intermediate goals' by the therapist. These intermediate goals will promote movement through life spaces increasingly further from a participant's home and towards their programme goal. These goals should be individually tailored to account for a participants prefracture abilities.

An example of a programme goal and related intermediate goals is specified in Box 1.

| Box 1: Example goals                                                                                      |                                                                                                                                                                  |
|-----------------------------------------------------------------------------------------------------------|------------------------------------------------------------------------------------------------------------------------------------------------------------------|
| Programme goal                                                                                            | Travel on public transport (10-minute walk to bus stop, 20-minute bus journey, 5-minute walk to restaurant) to meet family for lunch, return by car with family. |
| Intermediate goals
[figure not shown] | Walk to bus stop with the use of one crutch/stick, take bus to town and back independently.                                                                      |
|                                                                                                           | Walk to bus stop with the use of one crutch/stick, take bus to town and back with another person.                                                                |
|                                                                                                           | Walk continuously for 10-minutes outside with the use of one crutch/stick independently.                                                                         |
|                                                                                                           | Walk continuously for 10-minutes outside with the use of two crutches with another person.                                                                       |

The programme will be supported by a maximum of six therapist home visits (target mean of four) to enable a treating therapist to provide supervised support for practice and progression of intermediate goals. Therapists will employ motivational interviewing (engage, focus, evoke and plan) during supervised sessions (see 9.5.5.5).

The participant will be asked to practice independently and/or with family/friends between therapist visits. They will be asked to document this practice in a diary (whether completed or not, independently or with another person, how felt during and after).

The goal-orientated mobility programme targets behaviour change techniques related to capability

(*commitment, behavioural contract*), opportunity (*action planning, habit formation*), and motivation (*goal setting*) for outdoor mobility at increasing distances from home.

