| Study Duration                                         | 20 months                                                                                                                                                                                                                                                                                                                                                                                                                                                                                                                                                                                                                                                                                                                                                                                                                                                                                                                                   |
| Intervention                                           | Both groups will receive usual care. Participants allocated to the intervention will also 1) receive a goal-orientated outdoor mobility programme with up to six therapist home visits and four telephone/MS TEAMS sessions to support; 2) support to engage with community activities and social enterprise groups; 3) feedback and motivation for unsupervised mobility training; and 4) access to a video of older adults sharing their recovery experience after hip fracture.                                                                                                                                                                                                                                                                                                                                                                                                                                                          |

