# **7 Trial design & Flowchart**

## **7.1 Trial Design**

A multi-centre pragmatic parallel group (allocation ratio 1:1) randomised controlled assessor-blinded feasibility trial.

A schematic overview of the study is provided by Figure 1. A time/event matrix of trial procedures and stages is outlined in Table 1.

Both groups will receive usual care. In addition, the intervention group will receive a new outdoor mobility intervention. The intervention will start around 30 days after a participant returns home and end when their mobility end goal is achieved, six visits have occurred, or 12 weeks have passed – whichever comes first. This time frame/duration was selected as an appropriate window to target outdoor mobility based on our previous analysis of audit data, systematic reviews, and public and patient involvement focus groups. We aim to follow up all participants at 12 weeks post-randomisation. We will also follow-up participants to 6-months post-randomisation if the timing of randomisation permits this follow-up within the trial data collection window (to assess feasibility of longer-term follow-up within the current funding timeframe and budget).

The primary objective of this study (to determine whether the intervention can be delivered as intended considering the five domains of intervention fidelity) will be met by analysis of data collected through completed treatment logs and audio recordings during intervention delivery.

Secondary objectives of the study will be met by analysis of screening, approach, consent, and completion logs (secondary objective 3), descriptive statistical analysis of outcomes assessed at 6-weeks, 12-weeks, and 6-months post-randomisation (secondary objectives 1,4,5,7), and qualitative

interviews of patients and community team leaders and service managers and focus groups of therapists at intervention end (secondary objectives 1,2,3). The secondary objective to determine the count of AE and SAE will be met through reporting procedures in place from the point of randomisation to 12-week follow-up (secondary objective 6).

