#### **9.5.5.3 Motivation – additional professional support**

In between therapist home visits, the participant will be supported by up to four telephone/MS TEAMS calls. These calls will be structured around the participant diary and look to reinforce motivational interviewing strategies employed during supervised sessions. This additional support targets motivation through behaviour change techniques related to *feedback on behaviour, others monitoring with awareness*, and *self-monitoring* of both the behaviour and outcome of the behaviour.

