### **9.5.7 Outdoor intervention -example of schedule**

#### **• Telephone call 1**

- a. Set outdoor mobility programme goal using motivational interviewing (MI) strategies and behaviour change techniques (BCTs) (e.g. problem solving, action planning, information about health consequences, pros and cons, verbal persuasion about capability). The goal should require outdoor mobility, be meaningful to the patient, and achievable within the scope of the programme.
- b. Determine (logistically) what will be required to complete the outdoor mobility goal e.g. if the goal is to go for coffee with a friend how would they normally get there? Walk to the bus, travel ten stops, short walk to the café, then return. This will allow creation of intermediate goals.
- c. Schedule first home visit.

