- b. Discuss opportunities for community engagement e.g. previous activities or local community activities available through social enterprise groups. This should be guided by the participants interest and activities available in the local area (BCTs – action planning, social support, restructuring the social environment, verbal persuasion about capability).
- c. Remind of home visit plan.

• **Home visit 5**

- a. Discuss home diary – extent of practice, how felt during and after (MI strategies and BCTs e.g. feedback and monitoring, framing/reframing, verbal persuasion about capability).

- b. Practice intermediate goal while using MI strategies and BCTs (feedback and monitoring, framing/reframing, verbal persuasion about capability).
- c. Progress to next intermediate goal as deemed appropriate.
- d. Set plan for practice between home visits with social support as available (BCT – focus on past success, social support, restructuring the social environment, habit formation).
- e. Schedule next telephone call and final home visit.

• **Telephone call 4**

- a. Discuss home diary – extent of practice, how felt during and after (MI strategies and BCTs e.g. feedback and monitoring, framing/reframing, verbal persuasion about capability).
- b. Discuss opportunities for community engagement e.g. previous activities or local community activities available through social enterprise groups. This should be guided by the participants interest and activities available in the local area (BCTs – action planning, social support, restructuring the social environment, verbal persuasion about capability).
- c. Remind of final home visit plan.

• **Home visit 6**

- a. Discuss home diary – extent of practice, how felt during and after (MI strategies and BCTs e.g. feedback and monitoring, framing/reframing, verbal persuasion about capability).
- b. Complete programme goal while using MI strategies and BCTs (feedback and monitoring, verbal persuasion about capability, habit formation).
- c. Set plan for practice going forward with social support as available (BCT – focus on past success, verbal persuasion about capability, social support, restructuring the social environment, habit formation).

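### Fidelity is scored by session, so a participant who finishes at or before home visit 4 could miss the community-engagement component without lowering the score

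*Protocol*

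**What the plan says.** **Length of the programme.** Section 9.5.5.2 sets a "maximum of six therapist home visits (target mean of four"). Under Section 7.1 the programme is to "end when their mobility end goal is achieved", or at the sixth visit, or after 12 weeks, if either comes sooner.

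**The component.** The synopsis lists four elements of the intervention. The second is "support to engage with community activities and social enterprise groups". Section 9.5.5.4 describes the same support as part of the transition to independence and lets therapists give it at home visits or on calls, without naming a session. Section 9.5.7 is headed as an example and is the only session-by-session account in the Protocol. It brings the topic in at call 3 and repeats it at call 4: "Discuss opportunities for community engagement e.g. previous activities or local community activities available through social enterprise groups".

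**Fidelity.** Section 13.2 calls fidelity high when at least 80% of the manual's core components are fully delivered in each session, assessed on a random sample of recordings. The fidelity row of Figure 3 gives GO when at least 80% of sessions contained all components as described, AMEND at 51-79% and STOP at 50% or less.

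**Calls.** Section 9.5.5.2 says: "Participants will have a telephone call/MS TEAMS call with a therapist to set an outdoor mobility programme goal". Section 9.5.5.3 says: "In between therapist home visits, the participant will be supported by up to four telephone/MS TEAMS calls". The synopsis allows "up to six therapist home visits and four telephone/MS TEAMS sessions to support", and Section 16 gives the same totals. In Section 9.5.7, call 1 is the goal-setting call: "Set outdoor mobility programme goal using motivational interviewing".

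**The concern.** The primary objective is to establish whether the intervention was delivered as intended, and the fidelity row of Figure 3 carries that into the decision on a definitive trial. A measure built on sessions that took place cannot register content due in a session that never took place, nor content assigned to no session. Finishing early is part of the design here, and in the example schedule a named component sits late. The trial could report high per-session fidelity although some early finishers received no community-engagement support, and the figure would not show it.

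**Working it through.** **1. The plan's own count.** Writing C for calls and V for visits, Section 9.5.7 runs C1, V1, V2, C2, V3, V4, C3, V5, C4, V6. That is 6 visits + 4 calls = 10 contacts, which reproduces the maximum in the synopsis and Section 16.

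**2. Where the component falls.** Cutting that sequence at each possible last visit gives:

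| Last contact | Contacts | Calls | Contacts with community-engagement discussion |
|---|---|---|---|
| V1 | 2 | 1 | 0 |
| V2 | 3 | 1 | 0 |
| V3 | 5 | 2 | 0 |
| V4 | 6 | 2 | 0 |
| V5 | 8 | 3 | 1 |
| V6 | 10 | 4 | 2 |

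A participant with four visits who still receives call 3 would reach it. The zero applies when visit 4 or earlier is the last contact.

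**3. How many participants have four visits or fewer.** Let p be that share. Assume the mean is 4 and everyone has at least one visit. The remaining share, 1 - p, has at least 5 visits each, so

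4 ≥ 1·p + 5·(1 - p) = 5 - 4p, hence p ≥ 0.25.

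With 30 in the intervention arm, 0.25 × 30 = 7.5, so at least 8. The upper limit is 100%, when everyone has exactly four. The lower limit depends on the assumed minimum number of visits:
- minimum 0: 5 - 5p ≤ 4, so p ≥ 20%;
- minimum 2: 5 - 3p ≤ 4, so p ≥ 33%.

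The Protocol gives no distribution of visits. Two illustrative ones with mean 4 are uniform on 2 to 6, which gives 3/5 = 60%, and 1 + Binomial(5, 0.6), which gives 66%.

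**4. What the score does.** Take a participant whose last contact is V4 and whose sessions followed the example exactly.
- Each session scored against its own listed content: 6/6 = 100%.
- The participant scored against the four synopsis elements: 3/4 = 75%.
- Figure 3 read so that every session must contain every component: the video appears only in V1 and the community discussion only in C3 and C4, so 0 of the 10 listed sessions could qualify. Any trial following the example would fall under STOP however well it was delivered.

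The first reading is the workable one of the two per-session readings, and it cannot see the omission. Sampling recordings at random does not help, because only sessions that took place can be sampled.

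**5. Number of calls.** Added literally, Sections 9.5.5.2 and 9.5.5.3 allow 1 + 4 = up to 5 calls, or 6 + 5 = 11 contacts. The synopsis, Section 16 and Section 9.5.7 give 4 calls, or 10 contacts. In Section 9.5.7, call 1 precedes V1, where the diary is first handed out, so it cannot be one of the diary-based calls between visits. That leaves 3 of those.

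**The case against.** The strongest reply is that Section 9.5.5 governs and Section 9.5.7 only illustrates. Section 9.5.5.4 lets therapists give this support at any contact. The example also portrays a full six-visit course in which the programme goal is completed at visit 6, so someone who reaches the goal at visit 4 has already left the script, and a sensible therapist would bring the community discussion forward too. This stands against any prediction that the component will be missed. It does not answer the measurement point: permission to deliver at any time ties the component to no session, so a per-session score does not register its absence.

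Fidelity evidence is also wider than one percentage. It includes therapist questionnaires, participant interviews and focus groups, and these could bring an omission to light. They do not enter the fidelity row of Figure 3.

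Three stronger readings are tempting, and the documents do not support them:
- A reader might infer that a core component is missed. The core list is in the intervention manual, which is not shown. The Protocol only names the component.
- A reader might infer that the typical participant misses it. A target mean of four fits anything from 25% to 100% with four visits or fewer, and those participants miss it only if therapists treat the example as binding.
- A reader might infer that the call counts contradict each other. Three calls between visits satisfy a limit of up to four, and five is stated nowhere; it arises only by adding two sections. This is an ambiguity.

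A per-participant summary may already be planned in the manual or the statistical analysis plan, so its absence from the Protocol is not itself an error.

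**Conclusion.** The point holds as a blind spot in how the primary objective is measured. Under the two fidelity rules in the Protocol, an early finisher could go without a named component and still contribute a full set of faithful sessions: 6 of 6 if the last contact is visit 4, against 3 of 4 named components. At least 25% of participants (8 of 30) would have four visits or fewer, assuming the target mean of four is met, the maximum is six and everyone has at least one visit. How many of them would actually miss the component cannot be derived from the Protocol. The result also assumes that each session is scored against its own content, which the Protocol does not state. The question of whether there are four or up to five calls is a matter of clarification only.

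**What to change.** - Beside the per-session figure, report for each intervention participant whether each named component was delivered at least once before the programme ended, using the therapist questionnaires and treatment logs already planned.
- State whether each session is scored against its own expected content or against the full list of components.
- Confirm that the questionnaire is completed after calls. Section 9.5.5 asks for it after each session, while Section 12.1 says after each supervised session, and the example places the community discussion in calls.
- Reconcile Sections 9.5.5.2 to 9.5.5.4 with Section 9.5.7, the synopsis and Section 16 on whether the goal-setting call is among the four, and on how the transition component applies when the programme ends early. Which schedule is right is for the investigators to decide.

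The cost is some wording in the Protocol and manual and one derived tally. It needs no new form, provided the questionnaire records which components were delivered. The downside is that reported fidelity may look less favourable.

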#### **9.5.5.3 Motivation – additional professional support**

In between therapist home visits, the participant will be supported by up to four telephone/MS TEAMS calls. These calls will be structured around the participant diary and look to reinforce motivational interviewing strategies employed during supervised sessions. This additional support targets motivation through behaviour change techniques related to *feedback on behaviour, others monitoring with awareness*, and *self-monitoring* of both the behaviour and outcome of the behaviour.

#### **9.5.5.4 Transition to independence**

During home visits and/or telephone calls, therapists will plan for ongoing recovery after the goal-orientated mobility programme ends. This planning will include supporting participants to engage with their local community activities and social enterprise groups. The availability of activities and groups will vary according to the participants place of residence. The activities and groups of interest will be determined by the participant depending on their personal preferences, and should be reinforced by the therapist. This transition to independence targets motivation through behaviour change techniques related to *social support, action planning, verbal persuasion to boost self-efficacy*, and *restructuring of the social environment*.

